### Interventions

2.6

The acupuncture treatment protocol is based on the principles of Traditional Chinese Medicine and informed by literature review and expert consensus. Only licensed acupuncturists with over 5 years of clinical experience, will perform the interventions. Eligible patients will be randomized to receive either TA or SA intervention during the 4-week treatment phase, with three treatments per week (ideally every other day). Patients will lie flat on a treatment bed, and single-use sterile needles (0.30 mm diameter, 40 mm length; Hwato, Suzhou, China) will be applied.

#### TA group

2.6.1

Seven fixed acupoints will be used for the TA group (**Table 1**; **Figure 2**). *Baihui* (GV20) and *Sishencong* (EX-HN1) will target negative emotions (e.g., anxiety, depression), while *Tianshu* (ST25), *Zusanli* (ST36), *Shangjuxu* (ST37), *Sanyinjiao* (SP6), and *Taichong* (LR3) will address gastrointestinal symptoms. For abdominal and lower limb acupoints, the acupuncturist will insert needles into deep tissue layers. Following insertion, manipulations of twirling, lifting, and thrusting will be performed to achieve deqi (a sensation of soreness, numbness, distension, and heaviness) after sterilization. The needles will be retained for 30 minutes, with the deqi manipulation performed every 10 minutes during retention.

**Table 1 T1:** Locations of acupoints for acupuncture intervention.

Acupoint	Location
Baihui (GV20)	On the head, 5 cun^a^ directly above the midpoint of the anterior hairline
Sishencong (EX-HN1)	On the top of the head, 1 cun lateral to the Baihui acupoint in the front, back, left, and right directions, totaling 4 acupoints
Tianshu (ST25)	On the horizontal line of the navel, 2 cun beside the anterior midline
Zusanli (ST36)	3 cun directly below ST35, and one finger-breadth lateral to the anterior border of the tibia
Shangjuxu (ST37)	On the anterolateral aspect of the leg, 6 cun inferior to the ST35, and one finger-breadth lateral to the anterior border of the tibia
Taichong (LR3)	In the depression anterior to the junction of the first and second metatarsal bones
Sanyinjiao (SP6)	On the tibial aspect of the leg, posterior to the medial border of the tibia, 3 cun superior to the prominence of the medial malleolus

^a^
1 cun (≈20 mm) is defined as the width of the interphalangeal joint of the participant’s thumb.

**Figure 2 f2:**
[figure not shown]
Acupoint location. NA, non-acupoints.

#### SA group

2.6.2

For the SA group, 7 non-acupoints (NA) away from meridians and conventional acupoints will be used (**Table 2**; **Figure 2**). Superficial skin penetration (2–3 mm) will be performed at these points. Patients in the SA group will receive the same treatment duration as those in the TA group, with the deqi manipulation replaced by pretended manipulation every 10 minutes.

**Table 2 T2:** Locations of acupoints for sham acupuncture intervention.

Non-acupoint	Location
Non-acupoint 1	On the abdomen, 2 cun^a^ superior to anterior superior iliac spine, between the gallbladder meridian and the spleen meridian
Non-acupoint 2	On the abdomen, 2 cun inferior to navel, 1 cun beside the anterior midline, between the kidney meridian and the stomach meridian
Non-acupoint 3	On the lateral aspect of the leg, 3 cun inferior to GB34, between gallbladder meridian and bladder meridian
Non-acupoint 4	On the leg, 2 cun superior to the medial malleolus, in the middle of the medial tibia, between the liver meridian and the spleen meridian
Non-acupoint 5	On the leg, the midpoint of the line between GB40 and ST41, between the gallbladder meridian and the stomach meridian
Non-acupoint 6	On the head, 0.5 cun lateral to the midpoint of the anterior hairline
Non-acupoint 7	On the head, at the midpoint of the line connecting GB8 and TE20, between the gallbladder meridian and the triple energizer meridian.

^a^
1 cun (≈20 mm) is defined as the width of the interphalangeal joint of the participant’s thumb.

#### Rescue medicine

2.6.3

Participants will be instructed to maintain their usual diet and lifestyle throughout the study. When necessary, loperamide or polyethylene glycol 4000 will be permitted as rescue medication under the individualized guidance of a gastroenterologist. Furthermore, psychiatric specialists will be arranged to assess whether additional treatment is required based on patients’ scale scores and disease status, not limited to pharmacotherapy. Any use of rescue medication or other concomitant treatments will be documented, including measure, time and dosage.

### Outcomes

2.7

#### Primary outcome

2.7.1

The primary outcome will be the response rate, defined as the proportion of patients achieving a reduction of ≥50 points in the IBS-SSS (20) from baseline, which is recommended by the U.S. Food and Drug Administration (21). The primary endpoint will be the between-group comparison of response rate at week 4. The IBS-SSS consists of five items rated on a visual analog scale (0–100): severity of abdominal pain, frequency of abdominal pain, severity of abdominal distension, dissatisfaction with bowel habits, and interference with quality of life. Each item contributes equally to the total score, with an overall range of 0–500.

#### Secondary outcomes

2.7.2

Original IBS-SSS scores will be assessed as secondary outcomes at baseline and at weeks 2, 4, 8, and 12. The response rate will also be evaluated as a secondary outcome at baseline and at weeks 2, 8, and 12.

Hospital Anxiety and Depression Scale (HADS) (22). Symptoms of anxiety and depression will be assessed using the HADS at baseline and at week 2, 4, 8, and 12. The HADS is a validated 14-item instrument comprising two subscales for anxiety and depression. Scores are interpreted as follows: 0–7, no symptoms; 8–10, suspected symptoms; and 11–21, definite symptoms (23).

Visual Analog Scale (VAS) (24). The worst abdominal pain over the preceding 24 hours will be evaluated by VAS (0–10), with 0 indicating no pain and 10 indicating the worst imaginable pain. VAS will be evaluated at baseline and at week 2, 4, 8, and 12.

Satisfaction with bowel habits (25). Patients’ satisfaction with defecation will be assessed using a 7-point Likert scale, with response options ranging from “strongly disagree” to “strongly agree.” This scale provides an appropriate balance between sensitivity and usability, allowing for more nuanced assessment than a five-point scale while avoiding the cognitive burden of scales with more response options. Assessments will be conducted at baseline and at week 2, 4, 8, and 12.

Credibility/Expectancy Questionnaire (26). The credibility and expectancy to the intervention will be measured within 5 minutes after the first intervention session completed.

Blinding. The blinding assessment will be conducted by asking participants to guess their intervention allocation at week 2 and 4.

Safety. All adverse events occurring during the study will be monitored and recorded, regardless of their presumed relationship to the intervention. Adverse events will be classified according to severity and causality. Mild adverse events are those that do not substantially interfere with daily activities and require no specific treatment. Moderate adverse events involve noticeable discomfort or functional impairment and may require intervention. Severe adverse events are defined as life-threatening events, events resulting in significant disability, or those requiring hospitalization. For moderate adverse events, the decision to continue participation will be made in accordance with the patient’s wishes. Participants experiencing serious adverse events will be withdrawn from the trial and managed by the relevant clinical departments.

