### Study design

2.1

This will be a randomized controlled clinical trial involving patients with IBS. Eligible patients will be randomly allocated to the true acupuncture group (TA) or the sham acupuncture group (SA) in a 1:1 ratio. The 13-week study consists of a 1-week placebo run-in period, a 4-week treatment period and an 8-week follow-up. The study protocol was approved by the Medical Ethics Committee of Xiyuan Hospital, China Academy of Chinese Medical Sciences (Approval ID: 2025XLW019-1), and was registered (International Traditional Medicine Clinical Trial Registry: ITMCTR2025002100). The present trial will be performed following SPIRIT 2025 statement (Additional file 1). **Figure 1** shows the study flowchart. All personnel involved in this trial will receive standardized training on the trial procedures.

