#### Exclusion criteria

2.2.3

History of organic intestinal disorders, including inflammatory bowel disease, microscopic colitis, celiac disease, or Crohn’s disease;Diabetes mellitus and thyroid dysfunctions;Severe acute or chronic organic diseases, kidney or liver diseases;History of abdominal surgeries (including appendectomy, hemorrhoidectomy, and polypectomy conducted more than three months prior);Pregnancy or lactation;History of alcohol or drug misuse;Patients currently participating in other clinical trials.

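### A serious adverse event withdraws the participant from the whole trial, even in follow-up when no study acupuncture is left to stop, so some obtainable scores would be imputed (minor, cheap to fix)

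*Protocol article*

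**What the plan says.** The Safety paragraph of section 2.7.2 defines the top severity grade as life-threatening events, "events resulting in significant disability, or those requiring hospitalization". It then sets two rules for what follows an event:

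- Moderate: "For moderate adverse events, the decision to continue participation will be made in accordance with the" wishes of the patient.
- Serious: "Participants experiencing serious adverse events will be withdrawn from the trial and managed by the relevant clinical departments".

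The second rule is mandatory and carries no condition on causality or timing. The same paragraph records events of any cause throughout the study.

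Section 2.1 describes the study as "a 1-week placebo run-in period, a 4-week treatment period and an 8-week follow-up". Section 2.6 confines the assigned treatment to the first part after randomisation: "Eligible patients will be randomized to receive either TA or SA intervention during the 4-week treatment phase". Section 2.7.1 fixes the main comparison: "The primary endpoint will be the between-group comparison of response rate at week 4". Under section 2.7.2, IBS-SSS, HADS, pain VAS and bowel satisfaction are due at weeks 2, 4, 8 and 12.

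Section 2.11 analyses all randomised patients with baseline data and handles missing outcomes by multiple imputation. Section 2.5.1 permits unblinding when a serious adverse event makes the allocation necessary for clinical care.

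**The concern.** Stopping a treatment and leaving a study are different decisions. A serious event may well require the first; it does not by itself require the second. The rule makes no such distinction. After week 4 there is no study acupuncture to stop, so the only thing the rule can end is participation in follow-up.

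The planned analysis points the other way. It keeps these patients in the efficacy set, so their outcomes are wanted, but the withdrawal rule makes those outcomes missing for a reason tied to a clinical event. The measures are self-reported ("The IBS-SSS consists of five items rated on a visual analog scale"), and some of these patients could still complete them. At stake are a few observed values that would be replaced by imputed ones: possibly a primary outcome if the event comes before week 4, and only secondary data if it comes later.

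**Working it through.** **Reading the rule**

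1. The rule uses the word serious, whereas the paragraph defines severe. I take them as the same category. The definition includes any event that requires hospitalisation.
2. For moderate events the patient decides whether to go on participating. No such choice is given for serious events, so by contrast participation ends. No other section provides for assessment after withdrawal. That assessment stops is therefore an inference, though the plain one.
3. Treatment ends at week 4 and assessments run to week 12, so for 8 of the 12 post-randomisation weeks the rule has no study treatment to act on.

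**The plan's own figure**

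Section 2.10 gives 36 per group for response rates of 25% and 60%, two-sided α = 0.05 and 80% power. The pooled-variance formula gives 31 per group without continuity correction and 36 with it, so the figure reproduces. Allowing for 10% dropout: 36 / 0.9 = 40 per group, 80 in total. The allowance is 80 × 0.10 = 8 patients.

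**Assumptions (none from the documents)**

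- Serious-event rate of 0.5–5% over the 12 weeks, evenly spread. Exclusions such as "Severe acute or chronic organic diseases, kidney or liver diseases" point to the lower end.
- 50–100% of affected patients could complete the scales.

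**Patients affected**

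| Quantity | Formula | Low | High |
|---|---|---|---|
| Patients withdrawn | 80 × rate | 0.4 | 4 |
| Event before week 4 | × 4/12 | 0.13 | 1.33 |
| Event in follow-up | × 8/12 | 0.27 | 2.67 |
| Avoidable primary losses | before week 4 × 0.5 (low) or × 1 (high) | 0.07 | 1.33 |

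**Assessments lost per event** (visits at weeks 2, 4, 8 and 12)

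- Treatment period: (2 × 4 + 2 × 3) / 4 = 3.5
- Follow-up: (4 × 2 + 4 × 1) / 8 = 1.5
- Overall: (8 + 6 + 8 + 4) / 12 = 2.17

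Scheduled post-baseline assessments: 80 × 4 = 320.

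- Low: 0.4 × 2.17 × 0.5 = 0.43, or 0.1% of 320.
- High: 4 × 2.17 × 1 = 8.67, or 2.7% of 320.

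**Chance of at least one avoidable primary loss** (patients independent)

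- Low: 1 − (1 − 0.005/6)^80 ≈ 6%
- High: 1 − (1 − 0.05/3)^80 ≈ 74%

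The upper end needs both the 5% rate and every affected patient able to respond. At rates of 0.5–1% the expected avoidable primary loss is 0.07–0.27 of one patient.

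**Scale against the primary test**

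Losing one patient per arm at week 4 moves power, calculated without continuity correction, from 90.1% to 89.4% at 40 per arm, or from 86.8% to 85.8% at 36 per arm.

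**The case against.** The strongest objection is that the harm is inferred. The sentence sits in a safety paragraph and directs clinical care. What is collected after withdrawal is operational detail that a condensed article may leave to the full protocol. This stands as a caution: the article does not state that assessments cease. It does not remove the point, because withdrawal from the trial, with no limit by cause or period, is a stated rule and not a gap. If the full protocol defines withdrawal differently, this sentence should be brought into line with it.

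The second objection is size. The event rate is assumed, follow-up events cannot reach the week-4 endpoint, and the patients stay in the analysis set. All of that is right, and it limits the point to a minor one.

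Third, observing is not always clearly better than imputing. A patient unblinded under section 2.5.1 would give scores that are no longer blinded, and scores taken in hospital may reflect the acute illness rather than IBS. This also stands, and the amendment has to deal with it.

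Two stronger readings are tempting. A reader might infer that follow-up of the adverse event itself is cut short. The documents do not support that: the same paragraph monitors and records all events during the study and passes these patients to clinical departments. A reader might also infer that the rule biases the treatment comparison. Nothing in the documents shows more serious events in one arm or gives a direction.

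**Conclusion.** The point holds as a minor one. Read plainly, the rule ends outcome assessment for anyone with a serious adverse event, including in follow-up, and leaves some obtainable scores to imputation. The avoidable loss is at most a little over one primary outcome and under 3% of scheduled assessments, and more likely near the lower end of both ranges. It fits within the 8-patient dropout allowance, and no bias or material loss of power is demonstrated.

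The conclusion rests on three things: treating serious as the defined severe category, inferring that withdrawal stops assessment, and the assumed rates of events and of patients able to respond. The first two come from reading one paragraph; the last sets only the size.

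**What to change.** Replace the sentence in the Safety paragraph of section 2.7.2 with a rule to this effect: after a serious adverse event, study acupuncture is discontinued where clinically needed and the relevant department manages the patient; scheduled IBS-SSS, HADS, VAS and bowel-satisfaction assessments continue through week 12 where the patient is able and has not withdrawn consent.

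In section 2.11, state that the observed values are used in the modified intention-to-treat analysis and that only values that could not be obtained are imputed. Flag any assessment made after unblinding under section 2.5.1 and examine these in a sensitivity analysis.

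The cost is one or two sentences of amendment in each place, matching consent wording, and minor contact effort for a few patients. A few of the scores kept may be unblinded or coloured by acute illness. Sample size, endpoint and primary test do not change.

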### Data management

2.8

Paper-based materials will serve as the primary medium for data collection and storage. Clinical recruiters will be responsible for printing and archiving recruitment materials, case report forms, and informed consent documents. Acupuncturists and assistants will maintain treatment records and adverse event logs, which will be securely stored throughout the trial. To preserve blinding, research data will remain non-referential until all trial data have been collected and submitted to the principal investigator.

A standardized case report form will be established prior to enrollment, and data will be entered into EpiData software. Outcome assessors will record outcome data in the corresponding case report form sections. Any data modifications must be documented with reasons, timestamps, and signatures. Participant privacy will be strictly protected. Upon trial completion, data will undergo double entry and verification before database locking.

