#### Blinding

2.5.1

Due to the characteristics of acupuncture treatment process, only the acupuncturist and their assistant will have access to the randomization information. Patients, clinical recruiters, outcome assessors, data managers, and statisticians will be blinded to the group allocation. Unblinding of the study data will occur after the database has been locked and all participants have completed the trial.

Permitted circumstances for unblinding include (1): when a patient experiences a serious adverse event necessitating knowledge of the assigned intervention for clinical management (2); when the trial protocol contains major design flaws that threaten the scientific integrity of the results or constitute a hazard to participant rights and safety; and (3) legal requirements. If unblinding is necessary, the principal investigator will be immediately notified, and an assessment panel will evaluate the need for unblinding. If it is deemed necessary, the custodian responsible for safeguarding the randomization information will release the details according to established protocols, with the unblinding process carefully documented. The ethics committee will be informed upon completion of the unblinding.

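### Adverse events are logged by the only staff who know the allocation and who have no planned sessions in follow-up, so the recorded incidence is open to observer bias

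*Protocol article*

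**What the plan says.** Four statements in the protocol article bear on this point.

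- **Who keeps the log.** Section 2.8 (Data management): "Acupuncturists and assistants will maintain treatment records and adverse event logs".
- **Who knows the arm.** Section 2.5.1 (Blinding): "only the acupuncturist and their assistant will have access to the randomization information". The next sentence lists those kept blind: "Patients, clinical recruiters, outcome assessors, data managers, and statisticians will be blinded to the group allocation".
- **What is to be recorded, and when.** The safety paragraph of section 2.7.2: "All adverse events occurring during the study will be monitored and recorded, regardless of their presumed relationship to the intervention". It adds: "Adverse events will be classified according to severity and causality". It names nobody to do the classifying.
- **How long the study runs.** Section 2.1: "a 1-week placebo run-in period, a 4-week treatment period and an 8-week follow-up". Section 2.6 places the randomised sessions, three a week, in the 4-week treatment phase.

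Section 2.11 defines incidence as the number of patients with one or more adverse events divided by all patients. Section 2.8 has the blinded outcome assessors enter outcome data in the case report form. No section explicitly asks them, or any other blinded role, to enquire about adverse events.

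**The concern.** Safety is one of the trial's two stated aims (section 1 and the concluding paragraph of section 3). An event enters the incidence only if somebody asks about it or hears of it and then writes it down. All events count, whatever their cause, so the log depends on how actively staff enquire about complaints unrelated to needling. Staff who know the arm, and who deliver the intervention under test, may enquire or record differently between arms without meaning to. Section 3 lists the unblinded practitioner as a limitation but does not note that the same person keeps the safety log.

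There is also a question of timing. The log-keepers meet patients at sessions, and sessions stop at week 4. The recording promise extends to week 12. If recording relies on the session log, events in follow-up are less likely to reach it. No analysis can recover an event that nobody asked about.

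**Working it through.** **Is there a plan figure to reproduce?** The protocol article gives no expected adverse-event rate, so none exists for this point. The group size is needed only as a denominator, and it reproduces from section 2.10 (60% versus 25%, two-sided alpha 0.05, 80% power):

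- Pooled formula: n = [1.960 × √(2 × 0.425 × 0.575) + 0.842 × √(0.60 × 0.40 + 0.25 × 0.75)]² / 0.35² = 30.1, rounded up to 31.
- With continuity correction: (30.1/4) × [1 + √(1 + 4/(30.1 × 0.35))]² = 35.6, rounded up to 36 per group, as stated.
- With 10% dropout: 36/0.90 = 40 per group, 80 in total, as stated.

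**Step 1: set the roles side by side.**

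| Role | Knows the arm (2.5.1) | Explicit adverse-event task |
|---|---|---|
| Acupuncturist, assistant | Yes | Keeps the log (2.8) |
| Outcome assessor | No | None stated; records outcome data (2.8) |
| Recruiter, data manager, statistician | No | None stated |

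Section 2.5.1 also mentions a custodian of the randomisation information. No patient contact is described for that role, so it does not change the picture.

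**Step 2: set the contact periods side by side.** Sessions after randomisation: 3 × 4 = 12, all in weeks 1 to 4. Recording period after randomisation: 4 + 8 = 12 weeks. Weeks without a planned session: 8/12 = 67%. The scales are collected at weeks 2, 4, 8 and 12 (section 2.7.2), so follow-up contacts exist, but none is tied to adverse events.

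**Step 3: what differential logging could do (assumed rates).** Recorded rate = true risk × proportion captured. With the same true risk in both arms, full capture in one arm and partial capture in the other, the spurious difference is risk × (1 − capture):

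| True risk | Capture 80% | Capture 50% |
|---|---|---|
| 10% | 2 points | 5 points |
| 20% | 4 points | 10 points |
| 30% | 6 points | 15 points |

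In patients: 8 of 40 in each arm, with three quarters captured in one arm, becomes 8/40 = 20% versus 6/40 = 15%. The direction could be either way.

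**Step 4: what a stop in logging at week 4 would do (assumed).** Under a constant event rate with 12-week risk p, the 4-week risk is 1 − (1 − p)^(4/12). The share of affected patients whose first event falls after week 4 is 1 − (4-week risk)/p:

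- p = 10%: 1 − 0.0345/0.10 = 65%
- p = 20%: 1 − 0.0717/0.20 = 64%
- p = 30%: 1 − 0.1121/0.30 = 63%

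This is a worst case. It needs both a constant rate and a complete stop in logging, and the documents state neither.

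**The case against.** The strongest reply is that treating staff are the natural people to log needling events, because they see them directly. It also keeps needle-site information away from blinded assessors. True acupuncture goes deep with manipulation (section 2.6.1) and sham is 2–3 mm at other sites (section 2.6.2), so a description of soreness could reveal the arm. This stands, and it shapes the remedy: a question put by the assessor at week 2 could compromise the week 4 primary assessment.

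The second reply is that safety is listed under outcomes and outcome assessors record outcome data, so blinded recording may be intended. The log is not said to be the only source, and a journal article need not spell out who asks what at each visit. This stands in part. It prevents any claim that follow-up events will be lost, but it does not cancel the explicit assignment of the log to the two unblinded roles.

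Three stronger readings are tempting but not supported:

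- **That the acupuncturists grade severity and causality.** Section 2.7.2 names no grader, and the log assignment is in a different section. Grading also does not enter the stated incidence, which counts any event of any grade or cause.
- **That nobody is assigned to record events after the last session.** The acupuncturists remain the named log-keepers, and section 2.7.2 commits to recording throughout the study. What is missing is a planned contact between them and the patients.
- **That 67% measures lost events.** It is a share of calendar time. Needle-related events would be expected mainly around sessions.

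**Conclusion.** The point holds as a weakness in how adverse events are ascertained. As written, the log behind the between-arm incidence is kept by the only roles that know the allocation, so whether an event is counted is open to observer bias. Follow-up events may be under-recorded because those staff have no planned sessions in weeks 5 to 12.

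The size cannot be estimated from the documents. The 2 to 15 points and the 63% to 65% are illustrations on assumed risks, capture rates and timing; they are not evidence of actual bias. The primary endpoint and the sample size are unaffected. This is a cheap improvement to make before enrolment, not a flaw that threatens the main result.

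**What to change.** 1. Keep the acupuncturists' session log for needle-site events.
2. Add one standard open adverse-event question to the case report form at the existing assessments. At weeks 4, 8 and 12 the blinded outcome assessor asks it after all efficacy scales are complete. At week 2 the patient answers it on a form that the assessor does not see, so that the week 4 primary assessment stays blind.
3. State that the between-arm incidence is based on both sources together.
4. Name who classifies severity and causality: existing blinded study staff, working from records with needle-site details that could reveal the arm removed.

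The cost is a few minutes per visit and one form page, with no new visits or staff. A small risk remains that an answer at week 4 or 8 hints at the arm before the later secondary assessments.
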